## 5.2. Number of Participants

Up to ~~55~~70 subjects may be enrolled so that 48 subjects (LY3475766: 36, Placebo: 12) have sufficient evaluable data.

## 5.5. Justification of Dose

Doses of 10, 30, ~~450~~ and 1000 mg IV and 100, 300, and 600 mg SC LY3475766 were selected based on preclinical pharmacology and toxicology data.

## 6.1. Inclusion Criteria

[1b] female subjects must be of nonchildbearing potential and include those who are infertile due to surgical sterilization (such as hysterectomy, bilateral salpingectomy, bilateral tubal ligation, or bilateral oophorectomy with verbal confirmation from the subject), congenital anomaly such as Mullerian agenesis, or those who are postmenopausal, defined as:

- i. a woman at least ~~50-40~~ years of age with an intact uterus, not on hormone replacement therapy, who has had cessation of menses for at least 1 year or at least 6 months of spontaneous amenorrhea with a follicle-stimulating hormone level >40 mIU/mL; or

### 6.3.2. Caffeine, Alcohol and Tobacco

While confined at the CRU, subjects are required to adhere to the CRU smoking and caffeine policy during the inpatient treatment days. Subjects should otherwise not intentionally change their consumption of tobacco- or caffeine-containing products during the study.

No alcohol will be allowed during the 24 hours before and 72 hours postdose, and 24 hours before each CRU admission and each outpatient visit, and throughout the duration of each CRU visit. Between ~~CRU~~ visits, daily alcohol consumption should not exceed 2 units for males and 1 unit for females (a unit is defined in Exclusion Criterion [34], Section

## 7.1. Treatment Administered

The investigational product will be administered either via an SC injection or as a slow IV infusion (over at least 30 minutes for Cohorts 1 and 2, or at least 60 minutes for Cohorts ~~5 and~~ 6). For SC administration, LY3475766 and placebo will be administered at a maximum volume

of 2 mL per injection. A maximum of 46 injections may be necessary to achieve higher planned dose levels.

**Table GZEA.5. Treatments Administered Subcutaneously**

| Dose Level          | LY
Concentration
per Vial
(mg/mL) | Number of Vials   | Volume
per
Injection
(mL) | Number of
Injections | Total
Volume
of
Injection
(mL) |
|---------------------|--------------------------------------------|-------------------|------------------------------------|-------------------------|--------------------------------------------|
| LY 100 mg/PL        | 50                                         | 1.3               | 2.0                                | 1                       | 2                                          |
| LY 300 mg/PL        | 50                                         | 4 5 | 2.0                                | 3                       | 6                                          |
| LY 600 mg/PL | 50                                  | 10         | 2.0                         | 6                | 12                                  |

Abbreviations: LY = LY3475766; PL = placebo.

Injection site selected for SC administration should be the abdominal region approximately 5 cm from the umbilicus and the treatment has to be administered through the needle applied at approximately 45° with pinching of the skin. Because subjects may receive multiple injections per dose, each injection should be administered in a different abdominal quadrant in Cohorts 3 and 4 (rotating from right upper quadrant, to right lower quadrant, to left lower quadrant, to left upper quadrant), the quadrant used should be recorded at the time of the injection. For Cohort 5 where 6 SC injections are necessary, the injections should be administered into 6 separate regions of the abdomen: upper right, middle right (same level as umbilicus), lower right, lower left, middle left (same level as umbilicus), and upper left. Administering in a clockwise or counterclockwise direction should be considered to avoid injecting into the same location twice. The abdominal location for each injection should be recorded at the time of the injection. All injections should be performed within a total of 510 minutes. Subcutaneous administration of LY3475766 should be done by a limited number of individuals for consistency. The same type of syringe and needle should be used for all subjects to ensure all injections are delivered to a consistent depth target into the SC space.

#### 7.4.1 Dose Escalation

Dose-escalation decisions will primarily be based on available safety and tolerability data obtained up to Day 8 from Cohorts 1, 2, 5 and 6 and up to Day 15 from Cohorts 3, 4, and 5 (Section 10.3.6). Additionally, any available PK data may be used to guide dose selection or to determine if the number of doses to be studied may be reduced.

In addition to safety reasons, the sponsor may decide to stop further dose escalation if pharmacodynamic data obtained from the previous cohorts are considered sufficient.

#### 10.3.6. Data Review during the Study

Access to safety data will occur when at least 7 subjects have completed study activities through

- Day 8 in Cohorts 1, 2, ~~5~~ and 6, and
- Day 15 for Cohorts 3, 4, and 5.

Leo Document ID = 3dd20392-1052-416e-8870-e6f45180bafe

PPD

Approval Date & Time: 26-Aug-2020 12:14:59 GMT

Signature meaning: Approved

PPD

Approval Date & Time: 27-Aug-2020 17:00:10 GMT

Signature meaning: Approved

## 2. ABBREVIATIONS

Abbreviations pertain to the Statistical Analysis Plan (SAP) only (not the tables, figures and listings [TFLs]).

|                           |                                                                                                                                         |
|---------------------------|-----------------------------------------------------------------------------------------------------------------------------------------|
| AE                        | Adverse event                                                                                                                           |
| AOBPM                     | Automated office blood pressure monitoring data                                                                                         |
| AUC                       | Area under the concentration versus time curve                                                                                          |
| AUC(0-t last ) | Area under the concentration versus time curve from time zero to time t, where t is the last time point with a measurable concentration |
| AUC(0-∞)                  | Area under the concentration versus time curve from time zero to infinity                                                               |
| BQL                       | Below the lower limit of quantification                                                                                                 |
| C max          | Maximum observed drug concentration                                                                                                     |
| CI                        | Confidence interval                                                                                                                     |
| CRU                       | Clinical Research Unit                                                                                                                  |
| CSR                       | Clinical Study Report                                                                                                                   |
| ECG                       | Electrocardiogram                                                                                                                       |
| e.g.                      | For example (Latin: exempli gratia )                                                                                             |
| ICH                       | International Conference on Harmonisation                                                                                               |
| IV                        | Intravenous                                                                                                                             |
| LDL-C                     | Low-density lipoprotein cholesterol                                                                                                     |
| MAD                       | Multiple-Ascending Dose                                                                                                                 |
| PD                        | Pharmacodynamic                                                                                                                         |
| PK                        | Pharmacokinetic                                                                                                                         |
| QTcF                      | The QT interval corrected using Fridericia's formula                                                                                    |
| SAD                       | Single-Ascending Dose                                                                                                                   |
| SAP                       | Statistical Analysis Plan                                                                                                               |
| SC                        | Subcutaneous                                                                                                                            |
| SD                        | Standard deviation                                                                                                                      |
| TFLs                      | Tables, Figures, and Listings                                                                                                           |
| TG                        | Triglyceride                                                                                                                            |
| t 1/2          | Half-life associated with the terminal rate constant ( $\lambda_z$ ) in non-compartmental analysis                                      |
| t max          | Time of maximum observed drug concentration                                                                                             |
| ULN                       | Upper limit of normal                                                                                                                   |

### **3. INTRODUCTION**

This SAP has been developed after review of the Clinical Study Protocol (final version dated 27 June 2019), amendment (a) (final version dated 19 September 2019), amendment (b) (final version dated 12 December 2019), amendment (c) (final version dated 14 February 2020), amendment (d) (final version dated 27 August 2020), final SAP version 1 (dated 25 September 2019), and SAP version 2 (dated 04 September 2020).

This SAP describes the planned analysis of the safety, tolerability, pharmacokinetic (PK) and pharmacodynamic (PD) data from this study. A detailed description of the planned TFLs to be presented in the clinical study report (CSR) is provided in the accompanying TFL shell document.

The intent of this document is to provide guidance for the statistical, PK and PD analyses of data. In general, the analyses are based on information from the protocol, unless they have been modified with Eli Lilly and Company. A limited amount of information concerning this study (e.g., objectives, study design) is given to help the reader's interpretation. This SAP must be signed off prior to first subject treatment administration for this study. When the SAP and TFL shells are agreed upon and finalized, they will serve as the template for this study's CSR.

This SAP supersedes the statistical considerations identified in the protocol; where considerations are substantially different, they will be so identified. If additional analyses are required to supplement the planned analyses described in this SAP, they may be performed and will be identified in the CSR. Any substantial deviations from this SAP will be agreed upon with Eli Lilly and Company and identified in the CSR. Any minor deviations from the TFLs may not be documented in the CSR.

This SAP is written with consideration of the recommendations outlined in the International Conference on Harmonisation (ICH) E9 Guideline entitled Guidance for Industry: Statistical Principles for Clinical Trials and the ICH E3 Guideline entitled Guidance for Industry: Structure and Content of Clinical Study Reports.

### **4. STUDY OBJECTIVES**

#### **4.1 Primary Objectives**

- To assess the safety and tolerability of single intravenous (IV) and subcutaneous (SC) doses of LY3475766 in dyslipidemic but otherwise healthy subjects.

#### **4.2 Secondary Objectives**

- To characterize the PK of LY3475766 following single doses in dyslipidemic but otherwise healthy subjects.
- To characterize the PD of LY3475766 following single doses in dyslipidemic but otherwise healthy subjects.

### 4.3 Exploratory Objectives

- To explore the PD effect of LY3475766 on the lipid profile of single doses in dyslipidemic but otherwise healthy subjects.

## 5. STUDY DESIGN

This first-in-human study will investigate the safety, tolerability, PK, and PD of LY3475766 in dyslipidemic but otherwise healthy subjects (single-ascending dose [SAD]).

Figure GZEA.1. illustrates the study design.

[figure not shown]

Abbreviations: IV = intravenous; SC = subcutaneous; SR = safety review.

### Figure GZEA.1. Dose escalation for Protocol J1T-MC-GZEA.

This is a randomized double-blinded SAD design in dyslipidemic but otherwise healthy male and female subjects, investigating the safety, tolerability, PD, and PK of LY3475766 versus placebo.

Subjects will be enrolled in 6 cohorts:

- Cohort 1: 10 mg LY3475766 or placebo IV
- Cohort 2: 30 mg LY3475766 or placebo IV
- Cohort 3: 100 mg LY3475766 or placebo SC
- Cohort 4: 300 mg LY3475766 or placebo SC
- Cohort 5: 600 mg LY3475766 or placebo SC
- Cohort 6: 1000 mg LY3475766 or placebo IV

Doses and the number of cohorts may be adjusted based on ongoing review of the PK, safety, and tolerability data.

## 6. TREATMENTS

The following is a list of the study treatment names that will be used in the TFLs.

| Study Treatment Name | Treatment order in TFL |
|----------------------|------------------------|
| Placebo              | 1                      |
| 10 mg LY3475766 IV   | 2                      |
| 30 mg LY3475766 IV   | 3                      |
| 100 mg LY3475766 SC  | 4                      |
| 300 mg LY3475766 SC  | 5                      |
| 600 mg LY3475766 SC  | 6                      |
| 1000 mg LY3475766 IV | 7                      |

Placebo data will be pooled. The above dose levels will be updated on the TFLs for the actual dose received.

## 7. SAMPLE SIZE JUSTIFICATION

Up to 70 subjects may be enrolled so that 48 subjects (LY3475766: 36, Placebo: 12) have sufficient evaluable data.

The sample size is customary for Phase 1 studies evaluating safety and PK, and is not powered on the basis of statistical hypothesis testing.

Subjects who are randomized and who are discontinued from the study (providing that discontinuation was not as a result of a safety finding) may be replaced to ensure that enough subjects complete the study.

## 8. DEFINITION OF ANALYSIS POPULATIONS

The “Safety” population will consist of all enrolled subjects who took at least 1 dose of the study medication, whether or not they completed all protocol requirements.

The “Pharmacokinetic” population will consist of all subjects who received at least one dose of LY3475766 and have evaluable postdose PK data.

The “Pharmacodynamic” population will consist of all subjects who received at least one dose of LY3475766 and have evaluable postdose PD data.

All protocol deviations that occur during the study will be considered for their severity/impact and will be taken into consideration when subjects are assigned to analysis populations.

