### **10.3. Statistical Analyses**

Statistical analysis of this study will be the responsibility of Eli Lilly and Company or its designee.

Pharmacokinetic and PD analyses will be conducted on data from all subjects who receive at least 1 dose of the investigational product and have evaluable PK and PD data.

Safety analyses will be conducted for all enrolled subjects who took at least 1 dose of the study medication, whether or not they complete all protocol requirements.

Additional exploratory analyses of the data will be conducted as deemed appropriate. Study results may be pooled with the results of other studies for population PK analysis purposes to avoid issues with post hoc analyses and incomplete disclosures of analyses.

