|-------------------------------------|----------------------------------------------------------------------------------------------------------------------------------------------------------------------------------------------------------------------------------------------------------------------------------------------------------------------------------------------------------------------------------------------------|
| Ig                           | immunoglobulin                                                                                                                                                                                                                                                                                                                                                                                     |
| informed consent             | A process by which a subject voluntarily confirms his or her willingness to participate in a particular study, after having been informed of all aspects of the study that are relevant to the subject's decision to participate. Informed consent is documented by means of a written, signed, and dated informed consent form.                                                                   |
| interim analysis             | An interim analysis is an analysis of clinical study data, separated into treatment groups, that is conducted before the final reporting database is created/locked.                                                                                                                                                                                                                               |
| investigational product (IP) | A pharmaceutical form of an active ingredient or placebo being tested or used as a reference in a clinical study, including products already on the market when used or assembled (formulated or packaged) in a way different from the authorized form, or marketed products used for an unauthorized indication, or marketed products used to gain further information about the authorized form. |

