## 9. STATISTICAL METHODOLOGY

### 9.1 General

Data listings will be provided for all data that is databased. Summary statistics and statistical analysis will only be presented for data where detailed in this SAP. For continuous data, summary statistics will include the arithmetic mean, arithmetic standard deviation (SD), median, min, max and N; for log-normal data (e.g. the PK parameters: Area under the concentration

versus time curve [AUCs] and maximum observed drug concentration [ $C_{max}$ ]) the geometric mean and geometric coefficient of variation (CV%) will also be presented. For categorical data, frequency count and percentages will be presented. Data listings will be provided for all subjects up to the point of withdrawal, with any subjects excluded from the relevant population highlighted. Summary statistics and statistical analyses will generally only be performed for subjects included in the relevant analysis population. For the calculation of summary statistics and statistical analysis, unrounded data will be used.

Mean change from baseline is the mean of all individual subjects' change from baseline values. Each individual change from baseline will be calculated by subtracting the individual subject's baseline value from the value at the timepoint. The individual subject's change from baseline values will be used to calculate the mean change from baseline using a SAS procedure such as Proc Univariate.

Data analysis will be performed using SAS® Version 9.4 or greater.

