## 9.4 Pharmacodynamic Assessment

### 9.4.1 Pharmacodynamic Analysis

The following PD parameters will be listed and summarized by treatment and timepoint (as appropriate):

- Fasting lipid panel (TG, total cholesterol, low-density lipoprotein cholesterol [LDL-C] (direct assay from central lab), very low-density lipoprotein cholesterol [calculated], high-density lipoprotein cholesterol, non-high-density lipoprotein cholesterol [calculated], apolipoproteins [apoA-I, apoB, and apoC-III]), change from baseline (Day 1 predose) and percentage change from baseline.
- Fasting angiotensin-like protein 3/8 complex levels, change from baseline (Day 1 predose) and percentage change from baseline.

For the fasting lipid panel (except for apoB and angiotensin-like protein 3/8 complex levels), summary statistics will include arithmetic mean, standard deviation, geometric mean, CV%, median, minimum, maximum, Q1, Q3 (due to the distribution of the data). For apoB and angiotensin-like protein 3/8 complex levels, standard summary statistics will be presented.

In addition, a mixed-model repeated-measure model will be used to evaluate treatment effect for the parameters change from baseline LDL-C, TG, apoB and angiotensin-like protein 3/8. The model will include treatment, timepoint, and treatment by time point interaction as fixed effects, subject as a random effect and baseline as a covariate. An unstructured covariance structure will be used and a compound symmetric structure can be used if the model fails to converge.

Example of SAS code (for the change from baseline analysis) as follows.

```
proc mixed data=xxx;  
class treatment;  
model change = baseline treatment timepoint treatment*timepoint  
/residual ddfm=kr;  
repeated timepoint / subject=subject type=UN;  
lsmeans treatment*timepoint / cl pdiff alpha=0.1;  
ods output lsmeans=lsm diffs=estims;  
run;
```

For the above analysis, TG and LDL-C will be log transformed prior to analysis, and back-transformed to calculate percent changes from baseline.

Absolute and change from baseline arithmetic mean time profiles of the PD parameters will be produced.

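### As worded, the SAP's pharmacodynamic population excludes placebo, contradicting the protocol and the SAP's own pooled placebo arm

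*Combined protocol and SAP*

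**What the plan says.** - **SAP section 8** defines the PD population as "all subjects who received at least one dose of LY3475766 and have evaluable postdose PD data". The pharmacokinetic (PK) definition just above it has the same form. The Safety definition in the same section is worded by study medication, so it takes in placebo.
- **SAP section 9.1** ties outputs to populations: "Summary statistics and statistical analyses will generally only be performed for subjects included in the relevant analysis population".
- **Protocol section 10.3** has a different PD set: "Pharmacokinetic and PD analyses will be conducted on data from all subjects who receive at least 1 dose of the investigational product", with evaluable data. The synopsis agrees. Protocol Appendix 1 defines investigational product as "A pharmaceutical form of an active ingredient or placebo being tested or used as a reference in a clinical study", and so on.
- **SAP section 6** lists Placebo first of seven treatments for the tables and figures and adds: "Placebo data will be pooled".
- **SAP section 9.4.1** summarizes PD by treatment and timepoint and says that "a mixed-model repeated-measure model will be used to evaluate treatment effect for the parameters change from baseline LDL-C, TG, apoB" and ANGPTL3/8. The example code asks for "lsmeans treatment*timepoint / cl pdiff alpha=0.1".
- **SAP section 3** says the SAP supersedes the protocol's statistical considerations and that substantial differences will be identified. **SAP section 11** reports none.

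**The concern.** The PD definition decides who enters the summaries and the model for the secondary PD endpoints. Read literally, it removes the randomized comparator from a trial that protocol section 5.1 and SAP section 5 both describe as investigating PD against placebo.

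Placebo matters here because lipids can move for reasons other than drug. Subjects had to show fasting TG of 135 to 499 mg/dL at both screening and Day -1. They were then confined on standardized meals, to Day 4 in the IV cohorts and Day 8 in the SC cohorts, and could return to their usual diet afterwards (protocol sections 5.1, 6.1 and 6.3.1).

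Without placebo, each dose's change from baseline carries diet, confinement and time effects along with any drug effect. Dose-versus-dose differences cancel what two arms share, but they compare one active dose with another and not with no drug. Between an IV and an SC dose, the different length of confinement does not cancel either.

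**Working it through.** **1. Planned numbers.** SAP section 7 plans 48 evaluable subjects: 36 on LY3475766 and 12 on placebo. Protocol section 7.2 gives 3:1 allocation. Check: 48 × 3/4 = 36 and 48 × 1/4 = 12. Over six cohorts, 48/6 = 8, that is 6 active and 2 placebo if cohorts are equal. The plan's figures are reproduced.

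**2. Who qualifies under each text.**

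| Source | Criterion | Active | Placebo | Total |
|---|---|---|---|---|
| Protocol 10.3 with Appendix 1 | Investigational product | 36 | 12 | 48 |
| SAP 8, Safety | Study medication | 36 | 12 | 48 |
| SAP 8, PD | LY3475766 | 36 | 0 | 36 |

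The literal PD definition removes 12/48 = 25% of planned evaluable subjects, all of them placebo. LY3475766 cannot be read as loose wording for study drug, because section 8 uses the broader term for Safety and section 6 lists Placebo apart from every LY3475766 dose. For PK the restriction does no harm: protocol section 9.5.1 does not plan to assay placebo samples for drug.

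**3. Contrasts per timepoint.** The code in section 9.4.1 yields all pairwise differences.
- With placebo: 7 arms, 7 × 6/2 = 21 differences, 6 of them against placebo.
- Literal wording: 6 arms, 6 × 5/2 = 15 differences, none against placebo.

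**4. Timepoints affected (Schedule of Activities).**
- TG, LDL-C and apoB: Days 2, 3, 4, 8, 15, 22, 29, 43, 57 and 85, which is 10 post-dose days. With predose that makes 11, matching the 11 lipid samples in protocol Appendix 5. Placebo contrasts absent: 6 × 10 = 60 per parameter.
- ANGPTL3/8 after Day 1: Days 3, 8, 15, 29, 57 and 85, which is 6 days. Adding the Day 1 samples (3 for IV, 2 for SC) gives 9 and 8, matching Appendix 5. Placebo contrasts absent after Day 1: 6 × 6 = 36.

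**5. Precision, in SD units.** The documents give no SD or effect size. Assume equal cohorts, complete data and a single-timepoint ANCOVA. SE = SD × √(1/n₁ + 1/n₂); degrees of freedom = N − arms − 1 for the baseline covariate.
- Dose versus pooled placebo (6 v 12): SE = √(1/6 + 1/12) = 0.50 SD; df = 48 − 7 − 1 = 40; 90% half-width = 1.684 × 0.50 = 0.84 SD.
- Dose versus dose under the literal wording (6 v 6): SE = √(1/6 + 1/6) = 0.577 SD; df = 36 − 6 − 1 = 29; 90% half-width = 1.699 × 0.577 = 0.98 SD.

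The differences that remain are therefore less precise as well as lacking a placebo reference.

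**The case against.** The best case for the plan is that placebo was never meant to leave. Section 9.1 restricts analyses only generally, section 6 pools placebo with no exception for PD, section 9.4.1 speaks of treatment effect, and section 11 declares no change. The PD sentence mirrors the PK sentence and was probably carried over from it, though that is inference. The planned outputs are detailed in a separate shell document that is not available here. All this stands: the documents show a contradiction, not a settled decision to drop placebo.

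A reader might go further and infer any of the following. The documents do not support them.
- **Placebo vanishes from every lipid output.** Listings cover all subjects. Screening TG and LDL-C are summarized by treatment (SAP 9.2). Total cholesterol is in the safety chemistry panel (protocol Appendix 2), which is also summarized by treatment (SAP 9.5.3). But that panel's TG and LDL-C are footnoted to screening and Day -1, and apoB is not in it.
- **The PD code requests placebo contrasts specifically.** It requests all pairwise differences. The SAP names placebo as comparator only for the blood-pressure monitoring analyses (9.5.4).
- **The secondary PD objective cannot be met at all.** That objective is to characterize PD, its endpoints are changes from baseline, and the trial is not powered for hypothesis tests. Active arms down to 10 mg remain; protocol section 5.5 puts 10 mg at about half the dose projected to lower TG by less than 10%. This low-dose reference is useful but is not placebo.
- **Selection on high TG passes fully into the endpoints.** PD baseline is a separate Day 1 predose sample. That reduces regression to the mean without removing it, and does nothing about diet or time.

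**Conclusion.** The concern holds as a wrong stated rule that conflicts with the protocol and with other parts of the SAP. Followed literally, it takes the post-dose PD summaries and the mixed model from 48 to 36 planned evaluable subjects. It also takes the placebo contrasts from six per timepoint to none, on the days listed in the working. No other planned summary supplies a post-dose placebo result for TG, LDL-C or apoB.

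The documents do not establish that the final tables will omit placebo. They establish that a programmer who follows section 8 would omit it, while one who follows section 6 would not.

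The counts are planned evaluable numbers; up to 70 subjects may be enrolled. The precision figures rest on the assumptions stated with them. Restoring placebo does not remove every route effect: with equal cohorts, the pooled arm would mix 6 IV and 6 SC subjects with different lengths of confinement.

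**What to change.** 1. In SAP section 8, define the PD population as all subjects who received at least one dose of study medication (LY3475766 or placebo) and have evaluable postdose PD data. Leave the PK population LY3475766-only.
2. In SAP section 9.4.1, name pooled placebo as the reference and each dose against it, at each timepoint, as the contrast of interest, as section 9.5.4 does for blood pressure.
3. If excluding placebo is intended, declare and justify it in SAP section 11, which now says nothing changed.

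The cost is about two sentences. The schedule does not differ by treatment, so placebo samples are already collected and no new data are needed. The table shells should be checked against the corrected definition.
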